**Methods/design:**

This single-blinded randomized trial of 12 months duration will test the effects of ETL compared with alfacalcidol on LVH and cardiac fibrosis in maintenance hemodialysis patients with secondary hyperparathyroidism. Both treatment regimens will be titrated to equally suppress secondary hyperparathyroidism while alfacalcidol treatment causes an increase and ETL a decrease in FGF23, respectively.

Patients treated thrice weekly with hemodialysis for ≥ 3 months and ≤ 3 years with parathyroid hormone levels ≥ 300 pg/ml and LVH will be enrolled in the study.

The primary study endpoint is change from baseline to 12 months in left ventricular mass index (LVMI; g/m^2^) measured by cardiac magnetic resonance imaging. Sample size calculations showed that 62 randomized patients will be necessary to detect a difference in LVMI of at least 20 g/m^2^ between the two groups at 12 months. Due to the strong association of volume overload and LVH, randomization will be stratified by residual kidney function, and regular body composition monitoring will be performed to control the volume status of patients.

Study medication will be administered intravenously by the dialysis nurses after every hemodialysis session, thus omitting adherence issues.

Secondary study endpoints are cardiac parameters measured by echocardiography, biomarker concentrations of bone metabolism (FGF23, vitamin D, parathyroid hormone, calcium, phosphate, s-Klotho), cardiac markers (pro-brain natriuretic peptide, pre- and postdialysis troponin T) and metabolites of the renin–angiotensin–aldosterone cascade (angiotensin I (Ang I), Ang II, Ang-(1–7), Ang-(1–5), Ang-(1–9), and aldosterone).

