### Investigational products

The pharmacodynamics of ETL and cinacalcet are similar. They both cause rapid, dose-dependent decreases in circulating levels of PTH, FGF23, calcium and phosphorus in CKD patients.

A single intravenous dose of ETL can lower serum levels of PTH for up to 72 h in patients on hemodialysis. FGF23 levels decrease by over 30% at 24 h after a single 10-mg dose of ETL, while little or no effect is shown on 1,25(OH)_2_D levels in a study conducted by Martin et al. [51]. The most frequent treatment-emergent adverse event is a decrease in blood calcium [52]. ETL dosage should be between 2.5 mg and 15 mg three times a week. The starting dose is 5 mg three times a week. To achieve a target value of PTH (100–300 pg/ml), the dosage will be adapted every 4 weeks in steps of 2.5 or 5 mg during the titration phase. Serum calcium will be measured at every dialysis session. Target levels of serum calcium corrected for serum albumin are ≥ 2.08 mmol/l.

ALFA is an analogue of vitamin D3. ALFA can decrease PTH levels by ≥ 30% and increase FGF23 levels threefold [53]. In general, ALFA is a safe and well-tolerated established treatment for sHPT.

The starting dose is 1 μg, administered as an intravenous bolus three times a week at the end of hemodialysis. ALFA dosage should be at least 0.5 μg three times a week with no maximal dose. Titration will be performed in 0.5- to 1-μg steps at 4-week intervals, depending on PTH values and serum calcium and phosphate levels. The target value of PTH is equivalent to the ETL group. Serum calcium corrected for serum albumin should be no higher than 2.55 mmol/l and serum phosphate levels should be below 2.5 mmol/l.

The goal is to achieve a similar reduction in PTH in both study groups while FGF23 is elevated in the ALFA arm and suppressed in the ETL arm in order to analyze the causality of FGF23 reduction on LVH and fibrosis.

However, it is likely that the levels of PTH will vary, simply due to the different pharmacodynamics of the two drugs. Even though the dose of the study medication can be changed during the drug titration period as well as later on when necessary in order to reach target PTH levels, these adaptations are often limited by serum calcium and phosphate levels.

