### Statistical methods

Data will be described as means and standard deviation or medians and interquartile range for continuous symmetric and skewed variables, respectively. Distributions of the analyzed parameters will be visualized by boxplots and histograms.

The primary endpoint (change in LVMI from baseline to 12 months) will be analyzed by the analysis of covariance. The main variable in the model to be tested will be treatment group, which represents the treatment effect on change in LVMI 1 year after baseline between the two treatments. Baseline LVMI for each patient will be used as a covariate in the model and the interaction between treatment group and baseline LVMI will be included. Furthermore, to account for stratification during randomization, the stratification factors will also be included in the model. The secondary endpoints (changes in FGF23, s-Klotho, PTH, 25(OH)D, 1,25(OH)_2_D, proBNP, pre- and postdialysis TnT and RAAS metabolites) will be analyzed analogously. All analyses will be conducted according to the intention-to-treat principle. Two-sided *p* values lower than 0.05 will indicate statistical significance.

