### Sample size calculation

On the assumption, based on published data, that the mean LVM/BSA of hemodialysis patients determined by cMRI is 100 g/m^2^ with a standard deviation of 25 g/m^2^ [42] and an expected treatment effect of delta LVMI of 20 g/m^2^, 25 patients are needed per group to detect this difference with 80% power using a two-sample *t* test at an alpha level of 0.05. Assuming 10% attrition (drop out/loss to follow-up) within 1 year of follow-up, the final sample size in the intention-to-treat analysis will be 31 patients.

Patients receiving a renal transplant as well as those who become pregnant (which is unlikely due to the significantly reduced fertility of women under dialysis) will drop out of the study.

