## Discussion

In our proposed trial we will provide novel insights into the extent of FGF23-mediated cardiac remodeling in patients on chronic hemodialysis. We specifically hypothesize that treatment with ETL ameliorates pathological changes in the cardiac structure of dialysis patients with sHPT by suppression of systemic FGF23 levels.

The EVOLVE study investigated the effect of lowering FGF23 with the use of cinacalcet on cardiovascular mortality in 3883 hemodialysis patients with sHPT. They were able to show that a reduction in FGF23 of ≥ 30% after 20 weeks of therapy showed a trend towards a decrease in cardiovascular mortality, sudden cardiac death and heart failure [35, 57].

A small study conducted by Choi et al. described a significant reduction in LVMI and a significantly improved diastolic function, measured by echocardiography, in 12 hemodialysis patients treated with cinacalcet [58].

In our proposed trial we make use of the deviant influence of ETL versus ALFA on the serum levels of FGF23 since, as mentioned previously, calcimimetic drugs decrease FGF23 while vitamin D increases it. Consequently, we generated a human model to study the influence of changing serum FGF23 levels on cardiac structure using approved medication for sHPT. We established PTH target values of 100–300 pg/ml considering the Kidney Disease: Improving Global Outcomes guidelines in order to demonstrate the effect of FGF23 independent of PTH. Study medication will be provided intravenously, allowing a very consistent delivery of the drug. One of the most important advantages of the intravenous treatment is the elimination of possible noncompliance. Patient adherence to oral cinacalcet therapy is known to be very low [59]. Another major advantage of this study when comparing it to the trial by Choi et al. is the use of cMRI as the diagnostic tool for the quantification of left ventricular mass, lowering the inter- and intraobserver variability known from using echocardiography. cMRI provides accurate anatomic information that is in excellent agreement with autopsy results [60, 61]. It is also able to detect LVH in patients with seemingly normal echocardiographic results due to a geometric assumption-free quantification of left ventricular mass [62, 63].

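### The PTH-independent reading needs similar PTH in both arms, but PTH is given only a test for a difference, and a non-significant result cannot show similarity

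*Protocol article*

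**What the plan says.** Similar PTH is a premise of the design. The abstract states: "Both treatment regimens will be titrated to equally suppress secondary hyperparathyroidism". The Background says FGF23 will be modified under a PTH clamp and draws from this the ability to test causality. The Investigational products section repeats the aim: "The goal is to achieve a similar reduction in PTH in both study groups", with FGF23 raised in one arm and lowered in the other. The Discussion explains that the PTH target of 100–300 pg/ml was chosen "in order to demonstrate the effect of FGF23 independent of PTH".

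The analysis of PTH is one item in a list. The primary endpoint is analysed by ANCOVA on the change from baseline, with treatment, baseline value, their interaction and the stratification factors. Then: "The secondary endpoints (changes in FGF23, s-Klotho, PTH, 25(OH)D, 1,25(OH)_2_D, proBNP, pre- and postdialysis TnT and RAAS metabolites) will be analyzed analogously". The decision rule is common to all endpoints: "Two-sided *p* values lower than 0.05 will indicate statistical significance".

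Two other places bear on the point. Investigational products concedes that PTH will probably vary because the drugs act differently, and that calcium and phosphate often limit dose changes. Study endpoints lists the association of the biomarkers, PTH among them, with the cardiac changes as a secondary objective.

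**The concern.** PTH and FGF23 play opposite roles. The trial needs FGF23 to separate and PTH not to, yet both receive the same test of no difference. For FGF23, a small p value supports the design. For PTH, the design needs evidence that any gap is small, and a large p value is not such evidence: it can come from similar arms or from imprecise data. The noisier the PTH values, the more often the test is non-significant whatever the true gap. With very precise data the opposite can happen, and a trivial gap is flagged.

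What is at stake is the mechanistic conclusion. If the arms differ in achieved PTH, part of an LVMI difference could follow PTH rather than FGF23. The randomised comparison of ETL with ALFA on LVMI stays valid either way.

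**Working it through.** **Inputs from the protocol.** Two-sided alpha 0.05 (Statistical methods). 25 evaluable and 31 randomised per group (Sample size calculation). PTH target 100–300 pg/ml (Investigational products), so the range is 200 pg/ml wide and half of it is 100 pg/ml.

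**Assumptions.** No SD for PTH or its change appears anywhere, so a range is used. It stands for the residual SD after baseline adjustment. The 100 pg/ml gap is an illustration, not a threshold from the protocol.

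**The plan's own figure.** The protocol states "25 patients are needed per group to detect this difference with 80% power", "with a standard deviation of 25 g/m^2" and a difference of 20 g/m². The normal formula gives n = 2 × (1.960 + 0.842)² × 25² / 20² = 24.5, so 25 per group; exact noncentral-t power at 25 is 79.2%. The 25 reproduces. The step to 31 does not follow from 10% attrition (25 / 0.9 = 27.8, so 28), but that is a separate matter. Both 25 and 31 are carried below, so the result does not depend on it.

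**Probability that the PTH test is non-significant when the true gap is 100 pg/ml.** Standard error SE = SD × √(2/n); noncentrality = 100 / SE; df = 2n − 2; the probability comes from the noncentral t distribution.

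Example, n = 25 and SD 200: SE = 200 × √(2/25) = 56.6; noncentrality = 1.77; critical t (48 df) = 2.011; probability of non-significance 59%. The 95% CI half-width is 2.011 × 56.6 = 114 pg/ml.

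| Assumed SD (pg/ml) | 25 per group | 31 per group | 95% CI half-width, 25 / 31 |
|---|---|---|---|
| 58 | about 0% | about 0% | 33 / 29 |
| 100 | 7% | 3% | 57 / 51 |
| 150 | 36% | 27% | 85 / 76 |
| 200 | 59% | 51% | 114 / 102 |
| 250 | 72% | 66% | 142 / 127 |
| 300 | 79% | 75% | 171 / 152 |

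SD 58 is what patients spread evenly over the target range would give (200 / √12 = 57.7). The miss rate passes 50% at an SD of about 177 pg/ml with 25 per group and about 198 pg/ml with 31.

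**Log scale, 25 per group.** A true 1.5-fold PTH ratio (difference ln 1.5 = 0.405) is non-significant in 20%, 48% and 66% of trials at log-SD 0.5, 0.7 and 0.9.

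**Limits of the calculation.** It is a two-sample approximation and omits the carried-over term ("the interaction between treatment group and baseline LVMI will be included", here with baseline PTH). Unless baseline is centred, the treatment coefficient in that model is the gap at a baseline PTH of zero, although entry generally requires at least 300 pg/ml.

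**The case against.** The strongest reply is that the protocol never says a non-significant PTH test will be taken as equal PTH. That is correct. A reader might infer from the shared p < 0.05 rule that the authors would declare the clamp successful on p > 0.05, but the text does not say so, and it openly expects PTH to vary.

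A reader might also infer that the test would miss a gap of half the target range in most trials. The documents do not support that. It needs an SD above about 177–198 pg/ml, and none is given. If titration keeps most patients within 100–300 pg/ml, the miss rate is close to zero. Entry PTH of 300 pg/ml or more, with no upper limit in the listed main criteria, makes a large SD possible but not established.

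Third, the plan is not confined to one p value. The ANCOVA yields an estimate from which an interval follows, distributions will be plotted, PTH is measured throughout, and associations with cardiac change are an objective. All this is useful, but none of it provides a way to judge whether PTH was similar enough.

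Finally, a margin for a secondary biomarker may be left to an analysis plan that is not shown. Its absence alone would be no finding. What stands is that the protocol does fix a method for PTH, and that method does not match the stated aim.

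**Conclusion.** The point holds in conditional form. The FGF23-causality reading rests on similar PTH, and the one stated analysis of PTH cannot demonstrate similarity at any SD. For a true gap of 100 pg/ml, the chance of a non-significant result runs from 3–7% at SD 100 to 75–79% at SD 300. That range rests on assumed SDs, an illustrative gap and 25 to 31 analysed per group. The effect is confined to the mechanistic interpretation; the primary LVMI p value does not change. It should be corrected, because the repair uses PTH values already being collected and a criterion chosen after the results are known would carry little weight.

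**What to change.** In Statistical methods:

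1. Take PTH out of the list analysed in the same way as the primary endpoint.
2. Estimate the ETL/ALFA ratio of PTH over the visits from the end of titration (week 16) to month 12, on the log scale, adjusted for baseline PTH and the stratification factors. Report it with its confidence interval.
3. State that p > 0.05 will not be read as equal PTH.
4. Make any PTH-independence statement conditional on the size of gap that the interval excludes, preferably against a margin that the investigators justify and fix before the outcome analysis. Otherwise report the LVMI result as ETL versus ALFA.

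No margin can be taken from the documents, so its choice is open.

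The cost is a little more analysis, with no new patients or measurements, and a claim that is harder to earn. As an illustration only, require a 90% CI inside ratios of 0.67–1.5 with 25 per group. Truly equal arms would then pass on the month-12 value alone in 76% of trials at log-SD 0.5 and in 29% at log-SD 0.7. Averaging about nine visits at an assumed within-patient correlation of 0.5 multiplies the SD by √((1 + 8 × 0.5)/9) = 0.745 and raises these to 97% and 71%. A true 1.5-fold ratio would pass in at most 5%.

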### Study endpoints

The primary endpoint is the change in LVMI (quantified in grams per meter squared) from baseline to 12 months between the ETL and ALFA groups as assessed by cMRI.

Secondary endpoints are the change in left atrial diameter (measured in millimeters), the change in LVMI and left atrial diameter progression (percent), the difference in cardiac fibrosis and fibrosis progression as measured with noncontrast T1 mapping (milliseconds) and differences in cardiac function (ejection fraction, measured as percent) as well as wall motion abnormalities (percent change) as measured by cMRI and strain echocardiography after 1-year treatment with either drug. Other secondary objectives include changes in serum levels of FGF23, s-Klotho, PTH, 25-hydroxyvitamin D (25(OH)D) and 1,25-dihydroxyvitamin D (1,25(OH)_2_D), phosphate, calcium, pro-brain natriuretic peptide (proBNP), pre- and postdialysis troponin T (TnT) and the metabolites of the RAAS cascade (Ang I, Ang II, Ang-(1–7), Ang-(1–5), Ang-(1–9), aldosterone) under either treatment as well as their association with the abovementioned cardiac changes.

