### Data Safety Monitoring Board

An independent Data Safety Monitoring Board of the Medical University of Vienna will be convened to assess the safety of treatment as well as the superiority of one treatment over the other [54, 55]. Interim analysis will be performed by the board after the completed follow-up of 10 cases in each treatment group (one-third of the planned study population). The Lan and DeMets alpha spending method using O’Brien–Fleming type boundaries will be applied and the trial will be stopped if *p* < 0.000207 [56].

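### The flat p < 0.05 rule does not match the protocol's alpha spending at the interim look and covers about 23 secondary measures unadjusted; the first effect is negligible, the second is worth a wording change

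*Protocol article*

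**What the plan says.** Three sections of the protocol article bear on this.

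- **Statistical methods** describes the covariance analysis of the primary endpoint and says the secondary endpoints are handled in the same way. It then states that two-sided p "values lower than 0.05 will indicate statistical significance". It makes no exception for the final primary test and gives no ordering, adjustment or exploratory label for the secondaries.
- **Data Safety Monitoring Board** gives the board the task "to assess the safety of treatment as well as the superiority of one treatment over the other". The look is timed "after the completed follow-up of 10 cases in each treatment group (one-third of the planned study population"). On the method it says: "The Lan and DeMets alpha spending method using O’Brien–Fleming type boundaries will be applied". The stopping threshold is p < 0.000207. No final boundary is given.
- **Study endpoints** names one primary endpoint, the change in LVMI by cardiac MRI at 12 months. It then lists cardiac and laboratory secondaries, the laboratory ones "under either treatment as well as their association with the abovementioned cardiac changes".

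The **Sample size calculation** uses alpha 0.05 with no mention of the interim look.

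**The concern.** Alpha spending defines a pair of boundaries, one at the interim and one at the end, which together use 0.05. The protocol states the first. Its general significance rule then gives the whole 0.05 to the final test, so the two stated rules add to slightly more than 0.05.

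The same sentence also governs the secondary endpoints. Fibrosis, FGF23 and the renin-angiotensin metabolites carry the mechanistic argument of this trial, and all of them are secondary measures in 62 patients. If each may be labelled statistically significant at 0.05, some labels may be due to chance, and the text tells the reader nothing about how to weigh them.

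**Working it through.** **1. Reproduce the interim boundary.** Inputs from the Data Safety Monitoring Board section: O'Brien-Fleming-type spending and information fraction t = 1/3. Assumption: the function is applied to each side at 0.025 and then doubled.

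Two-sided alpha spent = 2 × 2[1 − Φ(z(1 − 0.05/4)/√t)]

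- z(0.9875) = 2.2414, and 2.2414/√(1/3) = 3.8822.
- 1 − Φ(3.8822) = 0.00005175, and 4 × 0.00005175 = 0.000207.

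This equals the stated threshold, so the interim figure is correct. It corresponds to |Z1| > 3.710.

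**2. Overall error if the final test stays at 0.05.** The interim and final statistics have correlation √t. Numerical integration of P(|Z1| > 3.710 or |Z2| > 1.960) at t = 1/3 gives **0.05007**. The crude upper bound is 0.05 + 0.000207 = 0.0502.

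**3. Matching final level.** Solving for the final critical value that restores 0.05 gives z = 1.9606, or two-sided **p < 0.0499** (0.04993).

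**4. Sensitivity to the information fraction.** The 20 patients at the look are 20/62 = 0.323 of those randomized, or 20/50 = 0.40 of the 25 per group required. With the interim boundary recomputed at each fraction:

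| t | Alpha spent at interim | Overall error if final test at 0.05 | Matching final level |
|---|---|---|---|
| 0.323 | 0.000159 | 0.05006 | 0.04994 |
| 1/3 | 0.000207 | 0.05007 | 0.04993 |
| 0.40 | 0.000788 | 0.05027 | 0.04973 |

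**5. Count the secondary measures in Study endpoints.**

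- Cardiac, 7: left atrial diameter (mm), LVMI (percent), left atrial diameter (percent), fibrosis, fibrosis progression, ejection fraction, wall motion.
- Laboratory, 16: FGF23, s-Klotho, PTH, 25(OH)D, 1,25(OH)2D, phosphate, calcium, proBNP, predialysis TnT, postdialysis TnT, and six analytes of the renin-angiotensin-aldosterone cascade.
- Total: 7 + 16 = 23, before any association tests.
- Statistical methods itself names 14: eight markers and the six cascade analytes.

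**6. Chance of at least one p < 0.05 when every null hypothesis is true.** For k independent tests this is 1 − 0.95^k. For correlated tests I assumed equal pairwise correlation ρ between normal test statistics. The protocol gives no correlations, so these are illustrations.

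| Tests | Independent | ρ = 0.3 | ρ = 0.5 | ρ = 0.7 |
|---|---|---|---|---|
| 14 | 51% | 44% | 35% | 25% |
| 23 | 69% | 58% | 45% | 31% |

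The expected number of false positives among 23 true nulls is 23 × 0.05 = 1.15, whatever the correlation.

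**The case against.** **The interim part changes almost nothing.** An excess of about 0.00007 at one-third information affects the conclusion only if the final p value lands between 0.0499 and 0.0500. Naming the Lan-DeMets method also implies a final boundary, and the 0.05 sentence may be only a general convention. This stands as to size. A reader might infer that the trial materially overspends its alpha; the arithmetic shows that it does not. What remains is that two stated rules disagree and the text does not say which governs.

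**Multiplicity of secondaries is usually left to the analysis plan, which is not shown.** Had the protocol been silent, that would settle it. It is not silent: it fixes a significance rule that covers these endpoints, and a later plan would have to override it.

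**The percentages are pessimistic.** This is largely right. Left atrial diameter appears in millimeters and in percent, LVMI percent change restates the primary, pre- and postdialysis TnT are one marker, and the cascade analytes move together. Nor is the global null expected for FGF23: the two drugs were chosen to move it in opposite directions. The independent-test figure is therefore an upper illustration.

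**Stronger readings that the document does not support.** A reader might infer that the rule declares all the secondary results significant; it only lets each be judged at an unadjusted 0.05. A reader might also infer that the secondaries raise the error of the primary claim; with a single primary endpoint they do not. The protocol makes no explicit confirmatory claim for any secondary measure.

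**Conclusion.** The point holds in a limited form. The flat 0.05 rule is inconsistent with the protocol's own alpha spending, but the consequence is minor: overall error 0.0501 instead of 0.0500 at one-third information, and at most 0.0503 over the fractions examined.

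The wider matter is that the rule attaches the label of statistical significance to about 23 secondary measures without adjustment or qualification. Under a global null the chance of at least one such label is 69% if the tests are independent and roughly 31% to 58% under the assumed correlations. Because some secondaries are expected to differ truly, these figures describe how little an isolated secondary p value below 0.05 would mean; they do not forecast this trial's results. The integrity of the primary test is not in doubt.

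**What to change.** Amend the decision rule in Statistical methods, or override it explicitly in the analysis plan:

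1. State that the final primary test uses the Lan-DeMets O'Brien-Fleming-type boundary computed at the actual information fraction of the interim look (about two-sided p < 0.0499 at one-third, 0.0497 at 0.40), and say which denominator defines that fraction.
2. Limit the statistical significance wording to the primary endpoint.
3. Report secondary endpoints and their associations with cardiac changes as estimates with 95% confidence intervals, labelled exploratory.

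Naming one or two secondaries in a fixed order after the primary would be an acceptable alternative if a confirmatory claim is wanted, but that is a preference, not a correction.

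The change affects wording only; no patients, visits or measurements are involved. The downside is a marginally stricter final threshold and fewer secondary results that can be called significant.
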